## Study design

This is a multicentre prospective observational study in which women will be consecutively recruited, with four centres currently recruiting:

- Tygerberg Hospital, Cape Town South Africa
- Fatima Memorial Hospital, Lahore, Pakistan
- Jinnah Hospital, Lahore, Pakistan

Clinical signs and symptoms experienced by the women prior to enrolment in this study will be centrally recorded via the online database Research Electronic Data Capture (REDCap) and used to identify the presence or absence of a unique clinical signature able to predict imminent eclampsia.

Chief investigators at each site will be responsible for training and familiarising recruiting and study staff with the use of the REDCap and online data collection via the supplied iPad.

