**Inclusion criteria**

*Eclampsia:*

- Diagnosed as new onset generalized tonic colonic seizures or coma in pregnant women or women who have recently given birth.
- Singleton pregnancies.
- All gestational ages, including post-partum eclampsia
- Enrolment to the study must occur within 7 days of an eclamptic episode
- Women must be coherent and able to provide informed consent prior to enrolment

*Preeclampsia:*

- Diagnosed as new onset of hypertension (>140 mmHg systolic or > 90 mmHg diastolic) after the 20th week of gestation and the coexistence of one or more of the following new onset conditions:
  - Proteinuria
  - Other maternal organ evolvement:
    - renal insufficiency (creatinine >90 umol/L)
    - liver involvement (elevated transaminases and/or severe right upper quadrant or epigastric pain)
    - neurological complications
    - haematological complications (thrombocytopenia, DIC, haemolysis)
  - Uteroplacental dysfunction
    - Fetal growth restriction
- All gestations >20 weeks
- Singleton pregnancies
- Have not experience an eclamptic episode

*Normotensive controls:*

- Healthy normotensive pregnant woman recruited from women seeking maternity services during the same or similar time period
- Matched by closest gestation and parity.

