## Outcome measures

The primary outcome is the presence or absence of a clinical signature of imminent eclampsia, unique both from women with preeclampsia and healthy normotensive pregnant women. To determine this, we have designed a standardised questionnaire collecting the following information:

| Maternal characteristics | Obstetric/booking information | Signs/symptoms | Eclampsia | Outcome |
| --- | --- | --- | --- | --- |
| First name | Gestation at booking | Highest systolic BP | Date of onset | Delivery date |
| Last name | Date at booking | Highest diastolic BP | Location of onset | Gestation at delivery |
| Maternal age | Estimated due date | Highest proteinuria | Prior magnesium sulphate | Indication for delivery |
| Address | How was due date estimated | Lowest platelet count |  | Mode of delivery |
| Race | Height | Highest AST |  | Live born |
| Marital status | Weight | Lowest haemoglobin |  | Sex |
|  | Antenatal care | Edema |  | Birthweight |
|  | Gravidity/parity | Tendon reflexes |  | Apgar at 5 minutes |
|  | Previous viable pregnancy outcome | Headaches, severity and onset |  | Neonatal outcome |
|  | Systolic BP at booking | Visual disturbances/type and onset |  | Number of days in hospital (maternal) |
|  | Diastolic BP at booking | Epigastric pain |  | Adverse maternal outcome |
|  | Proteinuria at booking | Tightness in chest |  |  |
|  | Antihypertensive medication | Shortness of breath |  |  |
|  | Tobacco/alcohol/drug use | Focal neurological deficit |  |  |
|  | Diabetes | Nausea/vomiting |  |  |
|  | Chronic hypertension | Confusion |  |  |
|  | Cardiovascular disease | Twitching/jerking of extremities |  |  |
|  | Anaemia | Mind state |  |  |
|  | HIV status | Concentration |  |  |
|  | Respiratory disease | Speech |  |  |
|  | Inflammatory bowel disease | Hearing |  |  |
|  | Autoimmune disease | Changes in moods |  |  |
|  | Malaria | Dizziness |  |  |
|  | Renal disease | Weakness or paralysis |  |  |
|  | Neurological disease | Jitters/nervousness |  |  |
|  | Medication use |  |  |  |

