## Statistical analysis

Data will be collected and analysed in clinically relevant categories with I2 or Mann-Whitney U tests used to detect difference between groups. We will compare data from women with eclampsia to those with i) preeclampsia and ii) normotensive pregnancies, to determine the unique signs and symptoms that precede eclampsia. Odds ratios will be used to determine strength of association for clinical characteristics significantly associated with eclampsia. We will also attempt to create a predictive score for eclampsia.

1. Knight M. Eclampsia in the United Kingdom 2005. *BJOG: An International Journal of Obstetrics & Gynaecology.* 2007;114(9):1072-1078.

3. Frias AE, Jr., Belfort MA. Post Magpie: how should we be managing severe preeclampsia? *Current opinion in obstetrics & gynecology.* 2003;15(6):489-495.

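### The symptom window runs to enrolment, after the seizure, so limb jerking during the fit or confusion after it can be counted as a warning sign of eclampsia

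*Protocol*

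**What the plan says.** Four parts of the Protocol bear on this point.

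- **Case definition** (Inclusion criteria, Eclampsia): "Diagnosed as new onset generalized tonic colonic seizures or coma in pregnant women or women who have recently given birth". Enrolment may follow up to 7 days after the episode.
- **Comparator definition** (Inclusion criteria, Preeclampsia): "Have not experience an eclamptic episode". The same list admits women to this group on the basis of "neurological complications".
- **Recording window** (Study design): "Clinical signs and symptoms experienced by the women prior to enrolment in this study will be centrally recorded".
- **Candidate signs** (Outcome measures, signs and symptoms column): "Twitching/jerking of extremities", confusion, mind state and speech are listed without timing. Two other entries do carry it: "Headaches, severity and onset" and "Visual disturbances/type and onset". For eclampsia itself the table lists a date of onset but no clock time.

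The intention is different from the recording window. Aim 1 concerns signs before the onset of eclampsia, and Statistical analysis compares the groups "to determine the unique signs and symptoms that precede eclampsia".

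**The concern.** A warning sign has to be observed before the event it warns of. Here the window closes at enrolment, which for a case comes after the event. Limb jerking is part of a tonic-clonic seizure, and a woman may be confused afterwards. If either is entered under the matching item, predictor and outcome are partly the same observation (incorporation bias). No comparator can supply such an entry, because by group rule she has had no eclamptic episode.

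This bears on the primary outcome, a signature that sets eclampsia apart from both comparator groups. Strength of association is to be judged by odds ratios, and a predictive score is to be attempted. A sign that is partly the seizure would look strong in both, yet give no lead time for the preventive treatment that the Background has in mind.

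**Working it through.** The Protocol gives no sign prevalence, sample size or power, so there is no figure to reproduce. The check compares the sections and then illustrates the size on assumed inputs.

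**1. The window against the aim**

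| Element | End of the window in cases |
| --- | --- |
| Aim 1; Statistical analysis | Before onset of eclampsia |
| Study design | Enrolment |
| Inclusion criteria | Enrolment up to 7 days after the episode |

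Under the Study design wording, the window in cases includes the seizure or coma and up to 7 days after it. In comparators it contains no such event.

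**2. Can the listed data separate the periods?** Headaches and visual disturbances have an onset entry. Twitching/jerking, confusion, mind state and speech have none. With only a date for eclampsia, the listed fields cannot place a same-day sign before, during or after the fit.

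**3. Which items overlap, and how?** Twitching/jerking overlaps with the content of the case-defining seizure. Confusion, mind state and speech overlap mainly through timing, as states that may follow the seizure.

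**4. Size, on assumed inputs.** Let p be the true pre-seizure prevalence, equal in eclampsia and preeclampsia, so the true odds ratio is 1. Let m be the share of cases without the sign in whom the seizure or its aftermath is scored as the sign. Then:

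- observed prevalence in cases = p + (1 − p)m
- observed odds ratio = [p + (1 − p)m] / [p(1 − m)]

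With p = 3%:

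| m | Observed in cases | Odds ratio |
| --- | --- | --- |
| 5% | 0.03 + 0.97 × 0.05 = 7.85% | 0.0785 / (0.03 × 0.95) = 2.8 |
| 10% | 0.03 + 0.97 × 0.10 = 12.7% | 0.127 / (0.03 × 0.90) = 4.7 |
| 20% | 0.03 + 0.97 × 0.20 = 22.4% | 0.224 / (0.03 × 0.80) = 9.3 |

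Simulated uncorrected chi-square tests at the 5% level, with assumed group sizes (cases vs preeclampsia), are significant this often:

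| m | 50 vs 200 | 80 vs 320 |
| --- | --- | --- |
| 5% | 36% | 51% |
| 10% | 74% | 90% |
| 20% | 99% | over 99% |

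**5. Sensitivity to the assumptions.** With p from 2% to 20% and m from 5% to 50%, the spurious odds ratio runs from 0.24 / (0.20 × 0.95) = 1.26 to 0.51 / (0.02 × 0.50) = 51. At p = 5% and m = 10% it is 0.145 / (0.05 × 0.90) = 3.2, with a 62% chance of significance at an assumed 100 per group. With m = 0 it returns to 1.0, which is what correct timing aims at.

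**The case against.** A reader might infer that these signs would be found unique to eclampsia by definition. The documents do not support that:

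- Twitching of the limbs is not a generalised seizure, and confusion is not coma. The problem arises only if the seizure or its aftermath is recorded as the sign.
- Women may enter the preeclampsia group through "neurological complications", so these signs can also be recorded there. The likely result is an inflated odds ratio, not guaranteed uniqueness.
- Nothing in the Protocol treats confusion as the beginning of coma, or says that twitching short of an eclamptic episode removes a woman from the preeclampsia group.

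It is also fair to say that the table gives topics, not question wording. The questionnaire is not shown, trained staff will administer it, and the stated intention is to capture signs before onset. The questions may already separate the periods. Nor can one claim that these items would have the largest odds ratios. Blood pressure, for example, separates cases from normotensive controls largely through the choice of controls.

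Finally, once the window is corrected, most of the problem goes, and a sensitivity analysis could be left to the SAP.

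These objections limit the strength of the claim but do not remove it. The one sentence that states the window places its end after the event, the item list has no timing for the signs most affected, and an analysis plan cannot restore timing that was never collected. Correcting the window also leaves a residue for jerking, because the start of a seizure is recognised by the jerking itself.

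**Conclusion.** The point holds as a conflict between the recording window and the aim, made worse by missing onset fields. The plan as written lets jerking during the fit and confusion after it count as warning signs, in cases only. Twitching/jerking is the item with direct overlap; confusion, mind state and speech are affected mainly through timing.

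The direction of the bias is clear: the odds ratio, and the item's weight in the score, are pushed upwards. The size is not known. The range of 2.8 to 9.3 rests on an assumed 3% background prevalence, an assumed true odds ratio of 1 and assumed misrecording in 5% to 20% of cases. It models one item against preeclampsia only. It shows that modest misrecording is enough to matter, not that misrecording at these rates will occur.

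**What to change.** 1. In Study design, define the window for cases as signs before the onset of the first seizure or coma, in line with Aim 1 and Statistical analysis. State the corresponding reference time for comparators.
2. Record onset for twitching/jerking, confusion, mind state and speech, as is done for headaches and visual disturbances. Record the time as well as the date of the first seizure or coma where it can be established.
3. Count twitching/jerking only when the woman or the chart describes an episode distinct from the first seizure and not running into it. Otherwise score it as not assessable.
4. Use the same item wording in the comparator groups.
5. Report the signature and the score with and without twitching/jerking, as a sensitivity analysis. The main claim need not rest on the version without it, since that could discard a genuine early sign in a study meant to find such signs.

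The cost is one corrected sentence, onset fields and revised wording for up to four items, and one extra analysis run. The small downside is that a true early twitch merging into the fit is not counted, but such a twitch gives little useful warning.

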## Ethical approval

Each site will be responsible for obtaining local ethical approval for this study, with recruitment only commencing once approval has been obtained and approval notification provided to the central chief investigator. All patients must provide informed written consent prior to enrolment in the study.

## Statistical analysis

Data will be collected and analysed in clinically relevant categories with I2 or Mann-Whitney U tests used to detect difference between groups. We will compare data from women with eclampsia to those with i) preeclampsia and ii) normotensive pregnancies, to determine the unique signs and symptoms that precede eclampsia. Odds ratios will be used to determine strength of association for clinical characteristics significantly associated with eclampsia. We will also attempt to create a predictive score for eclampsia.

1. Knight M. Eclampsia in the United Kingdom 2005. *BJOG: An International Journal of Obstetrics & Gynaecology.* 2007;114(9):1072-1078.

3. Frias AE, Jr., Belfort MA. Post Magpie: how should we be managing severe preeclampsia? *Current opinion in obstetrics & gynecology.* 2003;15(6):489-495.

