## Background

Eclampsia is a serious pregnancy complication that occurs when a pregnant woman - or new mother - experiences seizures associated with hypertension. These seizures pose a major risk to the life and the health of mothers and unborn babies. Signs or symptoms of severe preeclampsia are not always present or easy to recognise before a woman develops eclampsia. This is why it can be difficult to tell which women are likely to develop eclampsia before the first seizure occurs. If we can identify the features that are most common and unique to eclampsia, these could be used to develop a tool to help identify the women displaying signs or symptoms that occur prior to the onset of eclamptic seizures. This would mean that treatment to prevent seizures could be targeted to the right women and quickly administered before they become extremely unwell with this life-threatening complication.

The development of a tool to predict eclampsia in high-resource settings (such as Australia) has been largely hampered by the extremely low prevalence of this complication1. This makes it challenging for researchers in this setting to conduct impactful studies and obtain reliable and detailed information about the characteristic features of eclampsia. However, rates of eclampsia, like many other complications, are far greater in low to middle income countries (LMICs; including South Africa, Pakistan and the Solomon Islands), with an estimated 16-69 cases of eclampsia per 10,000 livebirths2,3. Thus, research conducted in LMIC settings allow for the prospective recruitment of a relatively large cohort of women with eclampsia. They are a useful target population to prospectively characterise the signs and symptoms preceding the disease. *Such characterisation may yield a unique clinical signature for eclampsia and the development of a predictive algorithm.*

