## Recruitment

Women presenting with eclampsia, preeclampsia or healthy pregnancies will be eligible to participate, with recruitment aiming to enrol *all women with eclampsia or preeclampsia at each site*.

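### The stated odds ratio is infinite for any sign that no comparator shows, and the plain chi-square test is unreliable for rare signs, so sparse tables need an exact test and an odds ratio that can handle a zero cell

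*Protocol*

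**What the plan says.** The Statistical analysis section of the protocol names its tools in one sentence: "I2 or Mann-Whitney U tests used to detect difference between groups". The printed symbol is most likely a chi-square sign lost in text conversion. The effect measure follows: "Odds ratios will be used to determine strength of association for clinical characteristics significantly associated with eclampsia". The section closes with an intention to attempt a predictive score and names no model for it.

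Two contrasts are planned: "We will compare data from women with eclampsia to those with i) preeclampsia and ii) normotensive pregnancies". Under Outcome measures, the signature must be "unique both from women with preeclampsia and healthy normotensive pregnant women". The Background describes the target as "features that are most common and unique to eclampsia".

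On numbers, Recruitment aims at "all women with eclampsia or preeclampsia at each site", and the Background gives "16-69 cases of eclampsia per 10,000 livebirths". Normotensive controls are "Matched by closest gestation and parity". The protocol states no group size, number of controls per case, preeclampsia incidence, significance level, continuity correction or rule for sparse cells.

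**The concern.** The outcome definition leads to the tables in which the two named tools are weakest. A sign that is unique to eclampsia has, by construction, few or no positives among the comparators.

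- **Estimation.** One zero cell makes the sample odds ratio infinite. Every sign absent from a comparison group then shares the same strength of association, whether one case or many cases had it. The measure cannot order these signs or supply weights for a score.
- **Testing.** For a rare sign in groups of very unequal size, expected counts among cases fall far below the level at which the chi-square approximation is trusted. A single observation may then cross 5%.

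At stake is how the study's strongest candidates are described, and whether some very rare signs pass the preeclampsia contrast by chance.

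**Working it through.** The protocol gives no sample size, power or error figure, so there is nothing of its own to reproduce.

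**Assumed inputs.** Two-sided alpha 0.05; n1 = 50 eclampsia and n2 = 200 preeclampsia (N = 250); chi-square without continuity correction. As for the 4:1 ratio, if all women with either condition are enrolled, the ratio follows incidence. With eclampsia at 16 to 69 per 10,000, a 4:1 ratio corresponds to preeclampsia at 4 × 16 = 64 to 4 × 69 = 276 per 10,000 (0.64% to 2.76%). If preeclampsia affected 2% to 8% (assumption), the ratio would lie between 200/69 = 2.9 and 800/16 = 50.

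**1. Odds ratio with a zero cell.** For a/n1 against 0/n2 the sample odds ratio is a × n2 / ((n1 − a) × 0), which is infinite for every a > 0 and every group ratio.

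The exact conditional lower 95% limit ψ does separate such signs. It solves P(all positives fall among cases | ψ) = 0.025.
- 1/50 vs 0/200: 50ψ/(50ψ + 200) = 0.025, so ψ = 5/48.75 = 0.10.
- 10/50 vs 0/200: C(50,10)ψ^10 / Σ C(50,k)C(200,10−k)ψ^k = 0.025 (sum over k = 0 to 10), so ψ = 10.5.

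The two signs share an infinite odds ratio but have lower limits of 0.10 and 10.5. Adding 0.5 to each cell also gives a finite value for the first: (1.5 × 200.5)/(49.5 × 0.5) = 12.2, 95% interval 0.49 to 303.

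**2. One case against none.**
- Uncorrected chi-square = N·n2/((N − 1)·n1) = 250 × 200/(249 × 50) = 4.02, p = 0.045. The statistic is close to n2/n1 at any study size, so it passes 3.84 at a ratio of about 3.84. The smallest expected count is 50 × 1/250 = 0.2.
- Yates: 250 × (200 − 125)²/(50 × 200 × 1 × 249) = 0.565, p = 0.45.
- Fisher: n1/N = 50/250 = 0.20.

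**3. Other sparse tables.**

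| Table | Uncorrected p | Fisher p |
| --- | --- | --- |
| 1/50 vs 0/500 | 0.0015 | 0.091 |
| 2/50 vs 1/200 | 0.042 | 0.103 |
| 1/50 vs 1/500 | 0.044 | 0.174 |
| 2/50 vs 0/200 | 0.005 | (50 × 49)/(250 × 249) = 0.039 |
| 3/50 vs 0/200 | 0.0005 | (50 × 49 × 48)/(250 × 249 × 248) = 0.008 |

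**4. Exact type I error of the preeclampsia contrast.** This sums binomial probabilities over all tables with p < 0.05, for 50 vs 200 and the same true prevalence in both groups.

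| Prevalence | Uncorrected | Yates | Fisher |
| --- | --- | --- | --- |
| 0.3% | 8.0% | 0.04% | 0.6% |
| 0.5% | 9.1% | 0.2% | 1.0% |
| 1% | 8.1% | 0.6% | 1.6% |
| 2% | 5.0% | 1.4% | 1.8% |
| 5% | 3.9% | 1.8% | 3.1% |

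From 0.3% to 1%, essentially all uncorrected false positives point towards eclampsia.

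**5. Both contrasts required.** Uncorrected test, 50 cases, 200 preeclampsia, equal prevalence in all three groups, number of controls assumed:

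| Controls | 0.3% | 0.5% | 1% |
| --- | --- | --- | --- |
| 50 | 0.001% | 0.009% | 0.09% |
| 100 | 0.7% | 1.2% | 1.5% |
| 200 | 4.7% | 4.1% | 2.5% |

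Equal prevalence is the favourable case. If the sign never occurs in normotensive women and 200 controls are taken, a single case already clears the control contrast (step 2), and the joint error returns to the 8 to 9% of step 4.

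**6. What zero of 200 allows.** The upper 95% limit is 1 − 0.05^(1/200) = 1.5%. A sign with true prevalence 0.5% is seen in none of 200 women with probability 0.995^200 = 37%.

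**The case against.** The strongest reply is that a short analysis section names families of tests, and that small-count rules, continuity corrections and zero-cell methods are commonly left to a statistical analysis plan, which is not at hand. This stands as a reason for modest severity. It does not dispose of the point, because the test and the effect measure are stated choices and the outcome definition itself produces the sparse tables.

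Four stronger readings are tempting and are not supported.

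- **One chance observation would be reported as a unique sign.** This needs the uncorrected statistic, a ratio near 4:1 or more, and success in the normotensive contrast as well. With 1:1 matching (assumed), one case against none gives p of about 0.31, and no joint error in step 5 exceeds 5% under equal prevalence.
- **Chi-square fails for what the study seeks.** The Background asks for signs that are common as well as unique. At 4:1 with no positive in preeclampsia, Fisher agrees from two cases onwards (0.039).
- **Near-exclusive signs cannot be ranked.** Only exact zeros are affected. For example, 2/50 vs 1/200 gives (2 × 199)/(48 × 1) = 8.3.
- **The score will not converge.** No regression model is named. Separation would arise only if the score were an ordinary maximum-likelihood logistic fit containing such a sign.

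**Conclusion.** The point holds in two parts of different strength. The odds-ratio part needs no assumption about group sizes or rarity: any sign absent from a comparison group has an infinite sample odds ratio, including a common sign that would be an ideal finding.

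The test part is conditional. With an uncorrected chi-square, alpha 0.05 and 50 vs 200, the type I error of the preeclampsia contrast is 8 to 9% at prevalences of 0.3 to 1%, and 5% or less at 2% and 5%. The normotensive contrast reduces the joint error by an amount that cannot be settled without the control ratio and the sign's frequency in controls. If Yates' correction is meant, the inflation disappears.

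Severity is minor to moderate: worth correcting because it is cheap, but no ground for saying that the main findings would be wrong.

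**What to change.** Amend the Statistical analysis section with three statements.

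1. Binary signs are compared with Fisher's exact test, or an exact unconditional test, whenever any expected count is below 5.
2. Odds ratios are exact or penalised (for example Firth) and reported with 95% intervals. If the predictive score is a regression, it is fitted with a penalty.
3. Where no woman in a comparison group shows a sign, the upper 95% limit of its prevalence in that group, 1 − 0.05^(1/n), is reported beside it, and the sign is not called unique without that limit.

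The cost is a few sentences and standard software; enrolment and data collection do not change. The price is conservatism: Fisher's test runs at 0.6 to 3.1% in the scenarios of step 4, so a few borderline rare signs will lose significance.

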## Data collection and management

Once eligible participants are identified, they will be provided with a patient information leaflet and invited to partake in the study. If written informed consent is provided:

1. Participant is enrolled in the study
2. Data will be collected by a trained research nurse or clinician (trained in interview techniques and the use of REDCap)
3. Data will be collected by directly asking the participant a series of standardised structured interview questions and review of medical charts
4. Participants will be followed until postpartum discharge, with maternal and neonatal outcomes recorded.
5. Using an iPad, all data will be entered into the secure online database REDCap, with each site having an individual database, with appropriate local translations.
6. All data will be accessible via the lead site and chief investigator.

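### The tests and odds ratios carry no site term and controls are not matched on site, so a difference between hospitals can appear as a sign of eclampsia

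*Protocol*

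**What the plan says.** **Analysis.** The Statistical analysis section names a categorical test (its symbol is garbled, probably chi-square), the Mann-Whitney test, odds ratios for features that reach significance, and an attempt at a predictive score. The contrast is: "We will compare data from women with eclampsia to those with i) preeclampsia and ii) normotensive pregnancies". Neither site nor country is mentioned at any step.

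**Sites.** Study design lists one hospital in South Africa ("Tygerberg Hospital, Cape Town South Africa") and two in Pakistan (one is "Fatima Memorial Hospital, Lahore, Pakistan"). The same sentence that introduces them reads "with four centres currently recruiting", yet three are listed.

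**Data capture.** Under Data collection and management, information comes from "directly asking the participant a series of standardised structured interview questions and review of medical charts". It is entered in REDCap, "with each site having an individual database, with appropriate local translations".

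**Who is enrolled.** Recruitment aims to take every eclampsia and preeclampsia case at each site, with no quota or ratio between them. Normotensive controls are "Matched by closest gestation and parity". They come from women using maternity services at about the same time, and the same hospital is not required.

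**The concern.** Site confounds a crude comparison when it is related both to group and to the feature compared. The plan leaves both links open.

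- **Site and group.** Because each hospital enrols what it sees, the ratio of eclampsia to preeclampsia follows its local case load. For controls, the matching rule does not tie a woman to the hospital of the case.
- **Site and feature.** Several questionnaire items are subjective and sensitive to wording, such as mind state, concentration, mood, dizziness and jitters. They are asked in different languages in different populations.

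The primary outcome is whether a signature distinct from both comparison groups exists. Features found significant go on to the odds ratios and may go into the score. A site artefact could therefore enter the main result, and a score built on it could partly predict the hospital rather than the seizure. Confounding in the other direction could hide a real within-site association.

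**Working it through.** The Protocol states no sample size, significance level, group ratio or symptom rate, so there is no figure of its own to reproduce. The check asks how far the crude test can err under assumed inputs when nothing is going on within any site.

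**Assumed inputs.** Three sites; eclampsia 60/70/70 (total 200); preeclampsia totalling 600, split in four ways; two-sided 5% level. The symptom rate is the same for eclampsia and preeclampsia within each site, so every site-specific odds ratio is 1. Rates by site are 40/50/50%, 30/50/50% or 30/60/60%, that is 10, 20 or 30 points apart.

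**Formulas.** Pooled rate in a group = Σ(nᵢ × pᵢ) / Σnᵢ. Crude OR = [P₁/(1−P₁)] / [P₀/(1−P₀)].

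**Worked case** (preeclampsia 400/100/100, rates 30/50/50%):
- Eclampsia: (60×0.30 + 70×0.50 + 70×0.50)/200 = 88/200 = 0.440.
- Preeclampsia: (400×0.30 + 100×0.50 + 100×0.50)/600 = 220/600 = 0.367.
- Crude OR = (0.440/0.560)/(0.367/0.633) = 1.36, against a true within-site OR of 1.00.

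The case ratio is 60/400 = 0.15 at the first site and 70/100 = 0.70 at the other two, a gap of 0.70/0.15 = 4.7-fold. The other splits follow in the same way: 0.20 v 0.467 (2.3-fold), 0.24 v 0.40 (1.7-fold), and 0.333 at every site (equal).

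**Simulated rejection rates** (20,000 studies per cell, Pearson chi-square on pooled data):

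| Preeclampsia by site | Gap in case ratio | 40/50/50% | 30/50/50% | 30/60/60% | Crude OR |
|---|---|---|---|---|---|
| 400/100/100 | 4.7-fold | 15% | about 45% | 79% | 1.16, 1.36, 1.56 |
| 300/150/150 | 2.3-fold | 8% | about 16% | 31% | 1.08, 1.18, 1.27 |
| 250/175/175 | 1.7-fold | 6% | 9% | 13% | 1.05, 1.10, 1.15 |
| 180/210/210 | none | about 5% | 4–5% | about 4% | 1.00, 1.00, 1.00 |

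The Cochran-Mantel-Haenszel (CMH) test stratified by site rejects in about 5% of studies in every cell.

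**Second model.** Two sites, 200 women per group, no within-site association:
- Symptom 50% v 30%, with 60% of eclampsia and 40% of comparison women from the first site: crude OR 1.18, simulated rejection 12%.
- Symptom 70% v 30%, shares 70% and 30%: crude OR 1.91, simulated rejection 91%.
- Equal shares, or equal symptom rates: crude OR 1.00.
- The stratified test stays between 5.1% and 5.4% throughout.

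Both models show the same condition: the bias needs a site difference in group mix and a site difference in the symptom rate. Either alone does nothing.

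**The case against.** **The section is short, and an unseen SAP may adjust for site.** This is fair. The Protocol does not use the word pooled. A reader might infer that it commits to ignoring site, but that goes beyond the text. What stands is that the methods it names are crude two-group comparisons and that its matching rule omits site. Matching is a design choice: a later analysis plan can adjust for site but cannot supply same-site controls that were never recruited.

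**A reader might infer that the comparison is confounded.** The document does not support this. Enrolling all cases permits unequal ratios between hospitals but does not establish them, and no symptom rate is given. The statement has to stay conditional.

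**Safeguards exist.** There is a standardised questionnaire, trained interviewers, chart review and site training. Separate databases do not themselves bias answers, and many features are measurements (blood pressure, proteinuria, platelets, AST, haemoglobin). These points reduce the risk, mostly for the measured items. They do not ensure equal reporting of subjective items across languages, and measured values can still differ between hospitals.

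**The large figures depend on a steep mix.** This is correct. The 79% needs a 4.7-fold gap in case ratio, for which the document offers no source. At 1.7-fold the crude test rejects in at most 13%.

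**Uniqueness requires a difference from both comparison groups.** Also correct. The three-site calculation covers the preeclampsia contrast only. Controls may in practice come from the same hospital, which would lessen the problem for the normotensive contrast but not for the other.

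**Conclusion.** The point holds in conditional form. As written, the tests, the odds ratios and the matching rule leave site uncontrolled in a study whose listed hospitals span two countries and several local translations. If group mix and symptom reporting both vary by site, a feature can be declared associated with eclampsia without any within-site association.

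The size cannot be taken from the document. Under the assumed 200 and 600 cases over three sites, it runs from no excess false positives to a rejection rate of 79%, depending mainly on how unequal the case ratios are. Site stratification keeps the rate at about 5% across that whole range, so the change is worth making without knowing which scenario applies.

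The mismatch between four stated and three listed centres is a separate inconsistency. It is not evidence of confounding, but it does mean that the statement about two countries covers only the listed hospitals, and that the strata are not yet fixed.

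**What to change.** 1. **Analysis.** State that the main comparisons are site-adjusted: either CMH for categories with van Elteren in place of Mann-Whitney, or logistic models with a site term. One coherent choice is enough. Report odds ratios from the same site-adjusted analysis.
2. **Controls.** Add site to the matching rule for normotensive women still to be enrolled. Controls already enrolled are covered by the analysis by site.
3. **Score.** Estimate predictor effects within site, for example by conditioning on site, and check that they are consistent across sites. Do not make study-site coefficients part of the score: a hospital outside the study has no such coefficient, and the tool is meant for use elsewhere.
4. **Separately,** reconcile the stated number of centres with the list in Study design.

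**Cost.** Site is already identifiable, because each has its own database, so the analysis change is a matter of wording with slightly less precision. The matching change is not only wording: it alters control selection a little at hospitals where recruitment is under way.
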